***- Methodology***

**- Eligibility criteria**

*Inclusion criteria*

Population: studies in which the general population participates.

Intervention: Studies whose objective has been to implement KT strategies in health that include audiovisual methods.

Comparator: studies whose objective has been to implement other KT strategies in health (written material, talks with health personnel, etc.).

Primary Outcomes:

− Health outcomes

− Quality of life

Secondary outcomes:

− Use of health services

− Costs, cost effectiveness

− Level of knowledge on the subject after the intervention

Studies

− Publication format: studies available as a complete publication.

− Language of publication: English or Spanish.

− Publication status: published studies, in press or gray literature.

− Publication date: without restriction

−Design: randomized clinical trials and observational studies that evaluate the effectiveness of different KT strategies in health.

*Exclusion criteria:* None.

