1. **Specific objectives**

- Determine the effectiveness of different strategies of social appropriation of knowledge through a systematic review of the literature.
- Based on scientific evidence and expert opinion, design 12 capsules of knowledge in maternal and neonatal health.
- Evaluate the effectiveness of the capsules in maternal and neonatal health in terms of social appropriation of knowledge, measured from attention, emotional response and recall through a pilot study, applying neuromarketing strategies.
- Produce a final version of the knowledge capsules in maternal and neonatal health with the design and content defined in the previous phases.

1. **Methodology**

The development of the project will be developed in 6 phases:

1. Systematic review of the literature.
2. Preliminary definition of the contents of the knowledge capsules in maternal and neonatal health.
3. Formal consensus of experts under the modified Delphi method where the content and strategies to be used in them will be defined.
4. Design and development of health capsules in maternal and neonatal safety.
5. Evaluation of the effectiveness of the knowledge capsules in maternal and neonatal health through a neuromarketing strategy, with a crossover experimental study.
6. Final production of health knowledge capsules in maternal and neonatal safety
7. **Phase 1. Systematic review of the literature and meta-analysis**

***- Design of the study:*** A Systematic Review of Literature (RSL) will be carried out, with the objective of reviewing and critically evaluating the literature on the effectiveness of different strategies in the transfer and social appropriation of knowledge in health. This RSL will include randomized clinical trials. In the event that this level of evidence is not found, we will proceed to look for cohort studies that evaluate this type of interventions in the general population.

***- Research question:*** the orientation of all steps in the development of the RSL, are within the framework of the following question:

In pregnant women, what is the effectiveness of KT strategies in health that include audiovisual methods, compared with other similar strategies (written material, talks with health personnel, etc.)?

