**− Data extraction and synthesis of the evidence**

The characteristics of the selected studies will be summarized using standardized formats. The data to be extracted in each study are:

- Study ID
- Year of publication
- Type of educational tool used
- Comparator
- Evaluated outcomes
- Results

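### The Phase 1 review question is about pregnant women, but eligibility is set on the general population and nothing later separates the two

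*Protocol*

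**What the plan says.** In the Protocol, Phase 1, the research question begins "In pregnant women, what is the effectiveness of KT strategies in health that include audiovisual methods, compared with other similar strategies". The sentence introducing it gives it authority over the whole review: "the orientation of all steps in the development of the RSL, are within the framework of the following question".

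The eligibility criteria that follow set a different population: "Population: studies in which the general population participates". Pregnancy is not mentioned among them, and the exclusion criteria are stated to be none. The design paragraph of Phase 1 likewise describes the fallback evidence, to be sought if no randomised trials are found, as "cohort studies that evaluate this type of interventions in the general population".

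The matching specific objective names no population at all: "Determine the effectiveness of different strategies of social appropriation of knowledge through a systematic review of the literature".

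**The concern.** Population is the first element of a review question, and here it is fixed twice, differently, without explanation. Phase 1 does not say, for example, that studies in other adults are admitted on purpose as indirect evidence. Two reviewers are to screen independently. One could apply the question and the other the criterion, and they would select different sets of studies while each followed the protocol.

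The review is the first link in the chain. Phase 2 builds the preliminary capsule content on its results, with pregnant women as the intended recipients. The Delphi panel in Phase 3 receives a synthesis of the review and meta-analysis, and Phase 4 draws on the review again. The Justification section argues that pregnancy adds neurophysiological complexity that bears on how knowledge is transferred. By that reasoning, an effect estimated in other adults cannot simply be assumed to carry over.

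**Working it through.** The protocol gives no figure for this point, so there is nothing to recompute. The check is to follow the population through Phase 1 and see whether any later step restores the restriction to pregnant women.

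1. **Question.** Pregnant women, and said to govern all steps.
2. **Design paragraph.** Cohort studies, the fallback, are to be in the general population.
3. **Inclusion criteria.** General population. The intervention and comparator criteria do not mention pregnancy either.
4. **Exclusion criteria.** None, so nothing narrows the criterion.
5. **Extraction.** The list introduced by "The data to be extracted in each study are" covers study identifier, year, type of educational tool, comparator, outcomes and results. No field is named for the participants or their pregnancy status.
6. **Pooling.** The Phase 1 statistical analysis combines trial results with fixed effects, or with random effects if I2 exceeds 40% or the chi-square p value is below 0.10. Switching to random effects changes the weights and the interval. It does not separate pregnant women from other participants.
7. **Secondary looks.** The one planned sensitivity analysis concerns risk of bias, and publication bias is assessed by funnel plot and Egger's test. No subgroup or restriction by population is planned.
8. **Quality of evidence.** GRADE will be used, but no instruction says how evidence from other adults is to be handled when the question is about pregnant women.

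Steps 2 to 4 admit a wider population than step 1 asks about. Steps 5 to 8 contain nothing that would recover the narrower one. Applied as written, the eligibility rule can therefore yield a pooled estimate for a mixed population, with no planned route to the effect in pregnant women.

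**The case against.** The strongest reply is that the protocol uses general population to mean the lay audience, as opposed to health professionals and decision makers. The problem description in the executive summary draws that contrast. The section on current approaches lists patients and the public as one audience beside providers and decision makers. The table of expected products names the general population, and chiefly pregnant women, as the target. On that usage pregnant women fall inside the criterion. This stands. A reader might infer that trials enrolling only pregnant women would be shut out, but the protocol's usage and the absence of exclusion criteria do not support that.

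A second reply is that the wider population may have been intended. The Phase 1 design paragraph uses it, the objective names no population, and Phase 5 enrols pregnant women, non-pregnant women and men. This also stands, and it means that restricting eligibility is not the only valid repair. It does not remove the contradiction: if the wider population was meant, the question is the text that needs changing.

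A third reply is that the review is preparatory. It does not enter the Phase 5 hypotheses or sample size. Its influence on the capsules is filtered by a ten-expert panel with an 80% agreement threshold and, in Phase 4, by neurocognitive theory. That limits the consequence. It does not justify leaving the review's population undefined.

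Finally, GRADE can rate evidence down for indirectness. That helps only if the reviewers know which studies are indirect, and neither the extraction list nor the criterion ensures that they will. A subgroup analysis might be left to an analysis plan, but the question and the eligibility criteria are protocol content. Both are stated here, and they disagree.

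**Conclusion.** The point holds as an internal contradiction that affects what the review estimates. The criterion is broader than the question, and as written the effect in pregnant women could not be separated from that in other adults.

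The size is unknown. It would depend on what share of the eligible studies are in pregnant women and on whether the effect differs between populations, and the protocol gives neither. A reader might infer that studies in other populations would dominate the pool, or that the review cannot answer its question at all. The documents do not support either inference: relevant trials remain eligible, and the mix of studies is not known in advance.

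The conclusion assumes that the extraction list and the Phase 1 analysis text are applied as they stand. It concerns Phase 1 and the use of its results in Phases 2 to 4. It does not touch the Phase 5 sample size or analysis.

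**What to change.** Reconcile the research question with the population criterion, and bring the fallback cohort sentence into line. Either of two routes is sound:

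- **Keep the question.** Make pregnant women the population of the primary synthesis. If studies in other adults are retained, synthesise them separately and label them as indirect evidence.
- **Widen the question to the general population.** Add a population field to the extraction list and prespecify a separate estimate for pregnant women. Use that estimate when the review informs Phases 2 to 4. If it is sparse, address the gap through the GRADE judgement on indirectness.

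The documents do not settle which population was intended, so the choice is for the investigators. The cost is a few lines of protocol wording and, on the second route (or on the first if other adults are kept), one extra extraction field. The downside is fewer studies, and so less precision, in the pregnant-women synthesis.

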**− Evidence search**

A systematic and exhaustive search of literature will be carried out.

*− Search in electronic databases*

To identify indexed publications, the following sources will be consulted:

− MEDLINE (Ovid platform)

− EMBASE (Ovid platform)

− LILACS (Virtual Health Library - VHL, iAHx interface)

− Cochrane Central Register of Controlled Trials – CENTRAL

− WHO International Clinical Trials Registry Platform ICTRP portal

− PsycINFO

− CINAHL

The search strategy will be composed of controlled vocabulary (MeSH, Emtree and DeCS) and free language. It will be complemented with expansion of controlled terms, truncators, proximity operators and Boolean operators to look for variations between the terms.

Searches will be conducted without language restriction.

**− Complementary search methods**

A "snowball" search will be conducted by reviewing the list of bibliographic references of the selected studies.

For each search a report will be generated, which will include the specific search strategy for each database, along with its results. Subsequently, duplicate references will be eliminated through the EndNote X6® program.

**− Screening of references and selection of studies**

Two reviewers will independently filter the references by their title and summary format and subsequently those that meet the defined inclusion criteria will be selected, after reviewing the full text of the publication. Any disagreement between the reviewers will be discussed as a group and a consensus will be reached regarding the inclusion or not of the studies.

**− Evaluation of the risk of bias of the selected studies**

The risk assessment of bias in the selected studies will be carried out using the bias risk tool of the Cochrane Collaboration for randomized clinical trials and using the SIGN tool for the identified cohort studies.

**− Assessment of the quality of the evidence set**

The quality of the whole of the evidence will be evaluated following the GRADE methodology and tables of evidence will be generated with the results obtained for each outcome found.

**− Data extraction and synthesis of the evidence**

The characteristics of the selected studies will be summarized using standardized formats. The data to be extracted in each study are:

- Study ID
- Year of publication
- Type of educational tool used
- Comparator
- Evaluated outcomes
- Results

**− Statistical analysis**

This will be done independently, both for randomized clinical trials and for cohort studies. In the case of clinical trials, the plan is to perform a statistical combination of the results of two or more individual studies identified through a meta-analysis, after screening for the presence of heterogeneity through the inconsistency test (I2), and the p value of the chi-square test, and if there is variation in the definition of the evaluated outcomes, statistical heterogeneity will be considered if an I2 greater than 40% or a p less than 0.10 is found in the chi-square test. The statistical combination of the results will be done through a meta-analysis of fixed effects or random effects if the data are heterogeneous. A sensitivity analysis will be carried out to study the influence of the risk of bias in the results of the meta-analysis. The presence of publication bias will be evaluated by means of a funnel plot and Egger's statistical test.

In the case of the cohort studies, the results of each outcome will be presented in the units of measurements reported in each study.

1. **Phase 2. Preliminary design of the contents of knowledge capsules in maternal and neonatal health**

Based on the results of the RSL, and following the methodologies described in the evidence for the development of the most effective KT strategies in health, the preliminary contents of the capsules will be designed, principally considering the key information for the preparation of the delivery and post-partum care which must be transmitted to pregnant women, which allows the generation of an adequate social transfer of knowledge. These contents will be defined in accordance with the domains described in the safe delivery checklist and will be designed for pregnant women who have a vaginal delivery as well as those who have a cesarean delivery.

These contents will be described independently, for the pre-partum, intra-partum and post-partum phase, and will include aspects related to patient safety, warning signs, interventions that will be received during delivery care and aftercare, both for normal delivery and for after surgery. It is proposed to make 2 capsules for each phase, one for each of the two possible means of delivery, for a total of 12 health capsules. The preliminary design of the 12 capsules will be carried out by the researchers of the group, and the proposal will be presented to the external experts in Phase 3.

1. **Phase 3. Formal expert consensus under the modified Delphi method**

The Delphi method is a structured consensus methodology that gathers and processes the opinions of experts on a specific problem, and by means of statistical resources builds a general group agreement [43]. This phase of formal consensus aims to validate the relevant contents of the 12 capsules with the experts.

*Sample size:* In this case, the sample size does not depend on the statistical power, but on the dynamics to reach a consensus within the panel. A minimum of 10 experts is recommended [44]. Ten experts will be convened in gynecology and obstetrics, psychology and health education, promotion and prevention programs, with at least 5 years of experience in maternal and perinatal health.

*Preparatory phase*

The members of the panel will be selected according to the previously defined profiles. A document synthesizing the identified evidence and the results of the RSL and meta-analysis will be prepared and the corresponding questionnaire will be designed for the consultation phase.

*Consultation phase*

In a first face-to-face meeting, the summary of the identified evidence will be presented to the panel of experts, as well as the preliminary content of the health capsules developed in the previous stage of the project.

Two additional consultation rounds will be held; for each of them, the statistical analysis will be performed, which will correspond to the description of measures of central tendency and dispersion and measures of position such as the median, based on a Likert scale that will be designed for that purpose [45].

After the rounds of consultation and statistical analysis, feedback on the processing of the results will be carried out.

*Consensus phase*

− Consensus building: a general group agreement or consensus will be defined, when there is a minimum agreement of 80% between the members of the panel.

− Report of results: A final report will be made that includes a detailed description of the process for each of its phases, the results of the statistical analysis and its interpretation, the difficulties presented during the process and the final result of the panel of experts.

1. **Phase 4. Design and development of health capsules in maternal and neonatal safety**

Based on the results of the systematic review of strategies for the transfer and social appropriation of knowledge, on the results of formal consensus of experts, and on the theoretical foundations of neurocognition and neuromarketing, the design of health knowledge capsules will be developed together with experts in health psychology, promotion and prevention in health, as well as experts in diagramming and development of audiovisual products. During this phase the final scripts, the graphic outline of the clips, their duration, the soundtrack and the production will be created, based on the results of the previous phases.

1. **Phase 5. Evaluation of effectiveness of knowledge capsules in terms of social appropriation of knowledge.**

A neuromarketing strategy will be applied in the Cognitive Neuroscience and Communication Laboratory of the National University of Colombia, with the objective of evaluating the effectiveness of the knowledge capsules in maternal and neonatal health in terms of social appropriation of knowledge, using measurements of attention, emotional response and remembrance.

The analysis will be conducted to find differences between subgroups or categories of educational level, defined as follows:

0 = No study

1 = Primary or Baccalaureate (basic education or secondary education)

2 = Higher Education (undergraduate and postgraduate)

*- Design:* Cross-over experimental study in which a group of pregnant women, non-pregnant women and adult men will be exposed to 13 clips, 12 of which will be produced through this knowledge transfer strategy and one will be an unrelated standard video that will be used as a control. The order of viewing the videos will be assigned randomly for each subject, so that each subject will have 13 evaluations. The random allocation tables will be generated by computer, and one will be made for each educational stratum (without education, with primary or secondary education, and with post-secondary education) and group (pregnant woman, non-pregnant woman and man). It is expected to have a minimum sample of 150 subjects.

*- Population and sample:*

- Inclusion criteria:

Pregnant women, non-pregnant women and men over 18 years of age, who agree to participate in the study through informed consent.

- Exclusion criteria:

participants who presented serious health problems linked to pregnancy or who presented any clinically significant visual and auditory problems, which affected the viewing of the videos.

*- Type of sampling:* not probabilistic, for convenience.

*- Sample size:*

Using the statistical analysis program for biomedical, social and behavioral sciences G * Power 3, the sample size was calculated for a one-way analysis of variance (ANOVA) design and fixed effects, using the F statistic. The selection of the parameters was made for the recall outcome, expecting that the differences of the capsules compared with the video control would be moderate. The parameters were therefore defined as follows: moderate effect size f = 0.3; power (1-β) = 0.90 and alpha (α) = 0.05 for three groups. The calculation yielded a result of 144 for the total sample. Considering that there would be no follow-up of the participants and the measurements would be taken in a single session, a low number of losses was estimated (mainly due to failures in the registry), so a minimum of 150 subjects was defined as a total sample, 50 for each group.

*Process:*

All participants will sign an informed consent (Annex 1) after explaining the objectives of the study and procedures that will be carried out. Participation will be completely voluntary.

The procedure consists of the projection of 12 health knowledge capsules of approximately 35 seconds each, and a control clip, not related to the subject. The control clip will be a standard video, which provides information on reproductive health and maternal safety, but which has not been designed based on evidence or following strategies based on neuromarketing.

The observation of the videos will be free; that is, they will not be explained to the participants during the screening, or the content of them. All the videos will be seen by the participants, but the observation of each one will be assigned in a random way.

The successive order of visualization of the videos is presented in Figure 1. It shows the successive ordering of the clips. However, the actual order of visualization of the clips will be done randomly for each of the subjects.

[figure not shown]

***Figure 1.*** *Form in which the assignment and evaluation of the effect of each intervention is planned.*

The process of consolidating results will be done for each clip as shown in Figure 2.

***Figure 2.*** *Selected sample, and methodological format of analysis of the clips*

During the screening of the health knowledge capsules, the eye tracking method will be applied to evaluate the attention of the subjects before the visual stimulus of the health capsules. By means of a Tobii TX 300 eye tracker and the Tobii Studio Software, the pupillary size in arbitrary units (AU), and the duration and direction of the fixation in seconds will be measured. Areas of interest will also be recorded, according to the stimuli in which the attention is fixed, the duration, and the order in which the visual exploration is performed.

The monitoring of the autonomous activity will be carried out through the registration of the electrodermal activity (Galvical Skin Reaction), which allows the evaluation the state or emotional reaction of the subjects. The record of electrodermal activity will be measured by the computerized psychophysiological recording equipment I-330-C2 + 12. (J & J Enterprises Seattle, WA). The measuring electrodes will be placed on the distal phalanx of the third and fourth finger of the non-dominant hand with SE-35 sensors connected to a T-601 preamplifier (J & J Enterprises Seattle, WA). For the analysis of results, the USE3 Software from Physiolab will be used (J & J Engineering, 2004).

The analysis of skin conductance data will be carried out with a procedure performed by Benedek and Kaernbach, through which the amplitude of the electrodermal response to a stimulus is obtained. Thus, two register values ​​will be recorded to calculate the amplitude: the conductance recorded in the lowest time of the latency period and the conductance peak. Subsequently, these values ​​and their registration will be subtracted. This analysis will be performed for each event identified in each capsule by each subject, to obtain an average of the conductance amplitudes for each grouping of images-events (positive, negative and neutral).

Between each video there will be a break of 5 to 10 seconds, and before starting the next video for evaluation there will be a neutral sequence in order to calibrate the response of the individual to a neutral state: this is considered to be the washout period between each video.

A parametrization of the measurements will be carried out in order to be able to relate both variables. Subsequently, a survey will be applied to evaluate the recall component.

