***Statistic analysis:***

Hypotheses raised:

- **Study hypothesis 1**

Comparison between capsules and video control

H0: μ capsule X = μ video control

Ha = μ capsule X ≠ μ video control

*μ = average attention, emotional reaction and recall*

- **Study hypothesis 2**

Comparison between groups: men, non-pregnant women, pregnant women

H0: μ1 = μ2 = μ3

Ha: ∃μj ≠ μ j = 1, 2, 3

*μ = average attention, emotional reaction and recall*

- **Study hypothesis 3**

Comparison between levels of schooling: none, primary, baccalaureate, undergraduate, postgraduate

H0: μ1 = μ2 = μ3

Ha: ∃μj ≠ μ j = 1, 2, 3, 4, 5

*μ = average attention, emotional reaction and recall*

- **Study hypothesis 4**

Comparison between family history: children, no children

H0: μ1 = μ2

Ha: μ1 ≠ μ2

*μ = average attention, emotional reaction and recall*

A descriptive analysis of the measured variables will be carried out. The qualitative variables will be described in proportions, and calculations for averages and standard deviation that follow a normal distribution will be performed for quantitative variables. For variables that do not follow this distribution, medians and interquartile ranges will be calculated. The normality of the variables will be evaluated by the Shapiro-Wilk test.

The difference between the averages of the variables of emotional reaction and attention will be carried out by means of an analysis of variance (ANOVA) for dependent samples, taking into account the effect of drag. For these comparisons, the non-parametric tests of Kruskal Wallis and the Wilcoxon rank sum will be used, according to the number of levels of each factor.

For the results of the survey, in which the recall of the contents of the capsules will be evaluated after their screening, an analysis will be made to compare the difference in proportions between the groups with a good level of recall and those with a low level of recall for each category of educational level.

Statistical software Stata 13.1 will be used to analyze the data.

1. **Phase 6. Final production of the health capsules in maternal and neonatal safety**

Professional experts in the layout and development of audiovisual animation products will carry out the final production process, taking into account the changes suggested by the analysis of results of the neuromarketing strategy.

- - - 1. **Ethical considerations**

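### Clip order is random for each subject with no balanced sequence set named; balanced orders and a position term would be a free improvement, not the repair of an error

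*Protocol*

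**What the plan says.** Phase 5 (Design) describes a cross-over in which participants "will be exposed to 13 clips, 12 of which will be produced through this knowledge transfer strategy"; the thirteenth clip is the control. On order it says "The order of viewing the videos will be assigned randomly for each subject", and the Process text repeats that "the actual order of visualization of the clips will be done randomly for each of the subjects". On the lists it says "The random allocation tables will be generated by computer, and one will be made for each educational stratum" and also for each participant group, which makes nine tables (three strata by three groups). No constraint on position or predecessor is named.

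For washout, the Process text says "Between each video there will be a break of 5 to 10 seconds", followed by "a neutral sequence in order to calibrate the response of the individual to a neutral state".

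The Phase 5 statistical section promises, for attention and emotional reaction, an "analysis of variance (ANOVA) for dependent samples, taking into account the effect of drag". It does not list the model terms. It then names Kruskal-Wallis and Wilcoxon rank-sum tests for these comparisons. Hypothesis 1 compares each capsule with the one control clip.

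**The concern.** Skin conductance, pupil size and fixation are recorded while 13 short clips follow one another in one sitting, so responses may drift with position or carry over from the clip before. The Protocol itself expects carry-over. If orders are drawn freely, chance alone decides how evenly each clip is spread over positions and predecessors. One control enters all 12 contrasts of hypothesis 1, so a chance displacement of that clip moves all 12 the same way. Drift that the analysis ignores also adds error to every within-subject difference. What is at stake is precision, and mainly in the smaller subsets; the validity of the comparison is not in question.

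**Working it through.** **Inputs.** From the Protocol, Phase 5: 13 clips, 150 subjects, 50 per group, nine allocation tables. Assumed: an even spread over the nine tables, 150/9 = 16.7, so about 17 per cell; a linear drift of D within-subject SDs from first to last clip; an independent uniform random order per subject.

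**The plan's own figure.** One-way ANOVA, three groups, f = 0.3, alpha 0.05, N = 144: noncentrality 144 × 0.09 = 12.96 on (2, 141) df gives power 0.9008. The stated 144 reproduces, and 150 gives 0.913. Clip order does not enter this figure.

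**Chance imbalance of position.** The position of one clip has variance (13² − 1)/12 = 14. The difference in position of two clips in one subject has variance 2 × 14 × (1 + 1/12) = 30.33, so SD 5.51. The mean gap between control and a capsule has expectation 0 and SD:

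- n = 150: 5.51/√150 = 0.45 positions
- n = 50: 5.51/√50 = 0.78
- n = 17: 5.51/√17 = 1.34

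The part shared by all 12 contrasts, the control's own mean position, has SD √(14/150) = 0.31.

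Simulation (3,000 sets of orders) agrees with these SDs. At n = 150 the control is expected 150/13 = 11.5 times at each position, with a typical minimum of 6 and maximum of 17. The largest of the 12 gaps has median 0.75 positions at n = 150, 1.3 at 50 and 2.3 at 17. Each ordered pair of neighbouring clips occurs about 11.5 times at n = 150 and practically none is missing. About 1.8% of pairs are missing at 50 and about 26% at 17.

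**Cost of random order when the analysis adjusts.** Efficiency of a clip contrast against the ideal variance 2σ²/n, with position and first-order carry-over in the model, averaged over 30 generated sets of orders. The Williams column uses permuted sets of 26 sequences cut at n.

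| n | Random order | Williams | Gain (points) |
|---|---|---|---|
| 150 | 98.0% | 99.3% | 1.3 |
| 50 | 95.1% | 99.2% | 4.1 |
| 17 | 87.2% | 94.8% | 7.6 |

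With position only in the model, n = 150 gives 99.3% against 99.98%.

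**Cost when position is ignored under random order.** The drift adds 30.33 × (D/12)² to a within-subject difference whose variance is otherwise 2, in units of the within-subject variance:

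- D = 1: 30.33 × (1/12)²/2 = 10.5%
- D = 2: 30.33 × (2/12)²/2 = 42.1%

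The standard error of a contrast at n = 150 is √(2/150) = 0.115 SD. A one-SD chance shift is 0.45 × D/12 = 0.037 SD (D = 1) or 0.075 SD (D = 2), about 0.32 to 0.65 of that standard error.

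**The case against.** The strongest reply is that this is a choice between two valid randomisations. Most of it stands.

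- *Bias.* A reader might infer that the control and capsules are systematically unbalanced. They are not: the expected gap is zero, any imbalance is chance, and the paired standard error already reflects it.
- *Simple randomisation.* The Protocol does not use that term. An independent draw per subject is the natural reading, but the text does not exclude a restriction within the tables, and Figure 1, on the assignment, is not available.
- *Weak handling of carry-over.* Random order does not cause this. At 150 subjects every predecessor pair is well represented and the efficiency loss against Williams is 1.3 points. The plan also has a break, a neutral sequence and a promise to account for carry-over.
- *The 10 to 42%.* It would be wrong to read this as the price of having no Williams design. It rests on an assumed drift and on an analysis that ignores position. A position term removes it under random order as well.
- *Missing model terms.* The Protocol does not say that position is left out, and terms may be set in an analysis plan that is not shown, so their absence is no fault. The rank tests it names, however, have no place for a position or carry-over term; where they are used, the order itself is the only protection.
- *Exact balance.* Predecessor balance is exact only in multiples of 26. None of 150, 50 or about 17 qualifies, and meeting it in all nine tables would take 9 × 26 = 234 subjects.
- *Cell size.* No education quota is set and sampling is by convenience, so 17 per cell is only illustrative. Hypothesis 1 is not framed within cells.

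**Conclusion.** This is a free improvement and not an error. Random order per subject is a sound, unbiased way to run the cross-over. Naming no balanced sequence set leaves position and predecessor to chance, and for the pooled comparison at 150 subjects this matters little: a gap SD of 0.45 positions and about 1 efficiency point after adjustment. The gain is about 4 points within a group of 50 and about 7 to 8 within a cell of about 17. This has some relevance because the Protocol aims to look for differences between education levels. These gains assume independent random orders and a model with position and carry-over; the cell figure also assumes an even spread over the nine tables. The larger benefit, avoiding a 10 to 42% variance inflation, belongs to the position term and depends on an assumed linear drift of 1 to 2 within-subject SDs, for which the Protocol gives no figure.

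**What to change.** Before the tables are generated:

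1. Within each of the nine planned tables, draw the orders from a Williams design for 13 clips (two 13 × 13 Latin squares, 26 sequences) in permuted blocks of 13, alternating the two squares. In any table each clip then falls at each position equally often, give or take one for an unfinished block. Predecessor balance is approximate, and exact only when a table completes a multiple of 26.
2. Record the position and the preceding clip for every viewing.
3. State that position enters the within-subject model for attention and emotional reaction. If rank tests are kept as the fallback, say that they do not adjust for position or carry-over.

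The cost is a different computer-generated list, two recorded fields and one model term. Participants, session time and procedures do not change.
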